#### Exploratory mechanistic outcomes

2.8.4

To explore potential biological correlates associated with acupuncture-related changes in depressive symptoms, this study will measure the following serum biomarkers: inflammatory cytokines (IL-6, TNF-α, hs-CRP), brain-derived neurotrophic factor (BDNF), and the kynurenine/tryptophan (KYN/TRP) ratio. Blood samples will be collected at two time points: baseline (W0) and within 24 hours of completing the 6-week treatment (W6). All blood draws will be scheduled between 8:00 and 10:00 AM. Participants will be instructed to fast overnight and to avoid strenuous exercise and alcohol consumption for 24 hours prior to sampling. Among these exploratory biomarkers, brain-derived neurotrophic factor (BDNF) is specified as the primary biomarker of interest, given its established relevance to both depressive symptoms and neuroplasticity in Parkinson’s disease. Inflammatory cytokines (IL-6, TNF-α, hs-CRP) and the kynurenine/tryptophan (KYN/TRP) ratio are considered secondary exploratory biomarkers, intended to provide complementary information on neuroinflammatory and metabolic pathways.

Concentrations of IL-6, TNF-α, hs-CRP, and BDNF will be measured using commercial ELISA kits. The KYN/TRP ratio will be analyzed via liquid chromatography–tandem mass spectrometry (LC-MS/MS). All samples will be processed (centrifuged and aliquoted) within 2 hours of collection, stored at –80°C, and analyzed in a single batch at the end of the study to minimize inter-assay variability. To account for multiple comparisons in exploratory biomarker analyses, false discovery rate (FDR) correction will be applied, and these analyses are intended for hypothesis generation rather than confirmatory inference.

### Safety evaluation

2.9

All participants receiving at least one intervention will be included in the safety analysis set. Safety monitoring and assessment will be conducted throughout the study. The research team will carefully document all adverse events (AEs), including common acupuncture-related reactions (e.g., local pain, subcutaneous hematoma, or syncope). For each AE, the team will evaluate and track its timing, severity, relationship to the intervention, and final outcome.

In the event of a serious adverse event (SAE)—defined as an event resulting in death, a life-threatening condition, requiring hospitalization, or causing significant disability—the research team will immediately discontinue the intervention, provide necessary medical care, and report the event to the ethics committee within 24 hours. As part of routine safety monitoring, vital signs (temperature, pulse, respiration, and blood pressure) will be recorded at baseline (W0) and Week 6 (W6).

Given the specific risks associated with this study population, the Columbia Suicide Severity Rating Scale (C-SSRS) will be used to systematically assess suicide risk during the screening period and at each follow-up point to ensure participant safety (36).

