### Study design

2.1

This study will be a single-center, prospective, evaluator- and statistician-blinded, two-arm, parallel-group randomized controlled trial (RCT) that will be conducted at the First Affiliated Hospital of Guangzhou University of Chinese Medicine. We will recruit 88 patients with PD-D, who will be randomly assigned in a 1:1 ratio to either the acupuncture treatment group or the waitlist control group.

All participants will maintain their stable, standard medication regimen throughout the study. A waitlist control design will be used to assess the add-on benefit of acupuncture. For ethical reasons, participants in the control group will be offered compensatory acupuncture treatment after the 6-week control period.

The study flow is illustrated in **Figure 1**, outlining the entire process from screening to follow-up. The schedule for all interventions, assessments, and follow-up visits is summarized in **Table 1**. Patients and the public were not involved in the design or conduct of this trial; however, results will be disseminated to participants in plain language after study completion.

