**Figure 1 f1:**
[figure not shown]
Study flowchart.

**Table 1 T1:** Schedule of enrollment, interventions, and assessments.

Study phase	Assessment content	Screening (W-1 ~ W0)	Baseline (W0)	Primary endpoint (W6)	Follow-up (W8)	Follow-up (W12)	Follow-up (W24)
Enrolment	Eligibility Screening & Informed Consent	✓					
	Demographic & Medical History Information	✓					
	Randomization		✓				
Assessment	MADRS	✓	✓	✓	✓	✓	✓
	HADS		✓	✓	✓	✓	✓
	MDS-UPDRS-III		✓	✓	✓	✓	✓
	PDQ-39		✓	✓	✓	✓	✓
	PSQI		✓	✓	✓	✓	✓
	PGIC			✓	✓	✓	✓
	ZBI		✓	✓	✓	✓	✓
	Acupuncture Expectancy Scale		✓				
	Blood Samples		✓	✓			
Safety	C-SSRS	✓	✓	✓	✓	✓	✓
	Vital Signs¹		✓	✓			
	Adverse Events/Concomitant Medications	✓	✓	✓	✓	✓	✓

¹Vital signs will be assessed at baseline (W0) and at the primary endpoint (W6).

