### Sample size

2.4

The sample size was estimated using an Analysis of Covariance (ANCOVA) for the primary outcome: the change in MADRS score from baseline (W0) to Week 6 (W6). Based on prior exploratory research (21) and the conversion formula by Leucht et al. (22), the pre-specified between-group difference (Δ) was set at approximately 2.4 points. An assumed common standard deviation (SD) of approximately 6.0 points for MADRS change scores was adopted, which is consistent with reported variability in previous studies of depression in Parkinson’s disease. This corresponds to a standardized effect size (Cohen’s d) of approximately 0.40. Statistical parameters were set at α = 0.05 (two-tailed) and a power of 1-β = 80%. The calculation, performed using G*Power 3.1 (23), indicated that 35 completers per group are required. To account for a potential 20% dropout rate, we plan to recruit 44 participants per group, resulting in a total sample size of 88. Although the primary analysis will use a mixed-effects model for repeated measures (MMRM), the sample size was estimated using an ANCOVA framework as a conservative approximation for the baseline-adjusted between-group comparison at Week 6.

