#### Waitlist control group

2.7.2

Participants in the waitlist control group will continue their stable, standard medication regimen for the 6-week study period. They will not receive acupuncture or any other study-specific interventions during this time. For ethical reasons, participants in the control group will be offered compensatory acupuncture treatment (using the same protocol as the acupuncture group) after the 6-week intervention period concludes.

To ensure comparability, all participants in both groups must maintain a stable antiparkinsonian medication regimen throughout the study. If any dose adjustments are necessary, they will be assessed by the investigator, documented in the CRF, and converted to the levodopa equivalent dose (LED) (26). No new systemic interventions that could potentially affect depressive symptoms will be permitted during the study. All changes in concomitant medications will be fully documented.

The use and dosage of antidepressant medications will be kept stable whenever possible throughout the 6-week controlled period. “Stable” is defined as no initiation, discontinuation, or dose change within 4 weeks prior to enrollment. During the trial, clinically indicated adjustments will be permitted for safety reasons or symptom worsening. All changes (type, dose, timing, and reason) will be documented and accounted for in the ITT analysis, with sensitivity analyses performed to assess robustness.

To monitor potential contamination during the waitlist period, at each assessment visit participants will be asked using a standardized checklist whether they have received any acupuncture or other non-study interventions for mood or motor symptoms (including acupuncture, electroacupuncture, moxibustion, rTMS, or psychotherapy) since the last visit. Any such use will be recorded as a protocol deviation (type, frequency, timing, and provider) and considered in the per-protocol and sensitivity analyses.

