## Discussion

3

This study aims to evaluate the efficacy and safety of acupuncture as an adjunctive therapy for patients with depression in PD-D. A key innovation of this trial is its systematic integration of multidimensional clinical outcomes with a panel of serum biomarkers reflecting shared pathological mechanisms: inflammatory cytokines, brain-derived neurotrophic factor (BDNF), and the kynurenine/tryptophan (KYN/TRP) ratio. This design is intended to facilitate a more integrated evaluation of acupuncture’s clinical effects and their potential biological correlates in PD-D, thereby enhancing the understanding of the potential neuro-immune-endocrine mechanisms underlying concurrent improvements in mood and motor function.

Depression in PD is not only highly prevalent but also strongly associated with motor impairment (39). Extensive neuroimaging and neurobiological studies indicate that the two conditions share highly convergent pathological mechanisms, including serotonin and norepinephrine system dysfunction, chronic neuroinflammation, hypothalamic-pituitary-adrenal (HPA) axis hyperactivation, and decreased brain-derived neurotrophic factor (BDNF) levels. This evidence suggests that interventions targeting only affective or motor symptoms in isolation are unlikely to break the maladaptive bidirectional relationship between them. Therefore, there is an urgent need for comprehensive intervention strategies designed to holistically modulate these shared pathological pathways.

Acupuncture, a safe and well-tolerated non-pharmacological therapy, has gained increasing attention in the comprehensive management of PD in recent years. Previous clinical studies have suggested that acupuncture can improve multiple non-motor symptoms in PD. Consistently, our earlier clinical studies also demonstrated that acupuncture effectively alleviates anxiety, improves sleep and gastrointestinal symptoms, and enhances UPDRS scores, thereby contributing to better overall quality of life in patients with PD (40–42).

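### Waitlist controls enter the safety set only if they later accept acupuncture, so the set lacks the full randomised comparator for Weeks 0 to 6

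*Protocol article*

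**What the plan says.** Section 2.9 (Safety evaluation) of the protocol article fixes membership of the safety set by receipt: "All participants receiving at least one intervention will be included in the safety analysis set". The same section adds: "Safety monitoring and assessment will be conducted throughout the study".

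The trial has two arms, with participants "randomly assigned in a 1:1 ratio to either the acupuncture treatment group or the waitlist control group" (section 2.1). Section 2.4 gives the size: "we plan to recruit 44 participants per group, resulting in a total sample size of 88". Of the controls during the six weeks, section 2.7.2 says: "They will not receive acupuncture or any other study-specific interventions during this time". Section 2.1 adds that "participants in the control group will be offered compensatory acupuncture treatment after the 6-week control period".

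Table 1 schedules the row "Adverse Events/Concomitant Medications" and the C-SSRS at every visit from screening to Week 24, with no restriction by arm. Safety is a declared aim beside efficacy. The Discussion puts it as follows: "This study aims to evaluate the efficacy and safety of acupuncture as an adjunctive therapy".

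The article gives no other safety population and describes no between-arm safety comparison. The intention-to-treat population in section 2.10 covers all randomised participants, but that section does not link it to the safety data.

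**The concern.** A receipt-of-treatment rule works when every arm receives something. Here one arm is a no-treatment waitlist for the whole of the only controlled period. Followed as written, the rule makes a control's membership depend on a decision taken after randomisation and after the primary endpoint.

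This matters because many of the safety events that section 2.3.3 anticipates can arise from the disease itself: suicide risk, injurious falls, hospitalisation for motor complications. Judging whether their frequency under acupuncture is unusual needs the concurrent randomised controls. If the controls in the safety set are only those who stayed and then chose acupuncture, the comparison is no longer between the groups that were randomised. Section 2.12 plans no data monitoring committee and no interim analysis, so the final safety tabulation carries more of the weight.

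**Working it through.** No stated figure is at issue. The check applies the membership rule to each arm and counts who qualifies.

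**Inputs**
- Planned arm size: 44 per group, 88 in total (section 2.4). This is consistent with the plan's own steps: 35 / (1 − 0.20) = 43.75, rounded up to 44; 2 × 44 = 88.
- Membership rule: at least one intervention received (section 2.9).
- Control exposure, Weeks 0 to 6: no acupuncture and no other study-specific intervention (section 2.7.2).
- Control exposure after Week 6: acupuncture offered, not required (sections 2.1 and 2.7.2).
- Uptake of that offer: not given. It is written below as *u*, the proportion of all 44 controls who receive at least one session, and varied over its full range as an assumption.

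**Step 1: what counts as an intervention.** Section 2.7.1 describes acupuncture as the intervention, given on top of standard drug treatment. Section 2.9 rates each adverse event for its relationship to the intervention and requires the intervention to be discontinued after a serious event. Both uses fit acupuncture and do not fit being on a waitlist. If background medication counted, the rule would exclude nobody, because section 2.3.1 already requires every participant to be on antiparkinsonian medication.

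**Step 2: acupuncture arm.** Anyone who attends at least one session qualifies: up to 44.

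**Step 3: control arm.** Nothing received before Week 6 qualifies a control. Membership comes only from a later session, so the number entering is 44 × *u*.

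**Step 4: size of the safety set**, taking all 44 in the acupuncture arm as treated:

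| Assumed uptake *u* | Controls entering | Safety set |
|---|---|---|
| 0% | 44 × 0 = 0 | 44 + 0 = 44 |
| 50% | 44 × 0.50 = 22 | 44 + 22 = 66 |
| 80% | 44 × 0.80 = 35.2, rounded to 35 | 44 + 35 = 79 |
| 100% | 44 × 1.00 = 44 | 44 + 44 = 88 |

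**Step 5: which controls are lost.** Those who decline the offer, and those who leave the study before receiving any session. Section 2.3.3 lists serious adverse events, marked worsening on MADRS and emergent suicide risk among the grounds for withdrawal, next to poor adherence and missed visits. A control withdrawn for a safety reason before any session is therefore outside the set. The article does not say how many such controls there would be.

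**Step 6: what is unsettled for those who enter.** Section 2.9 says who is in the set but attaches no period. For a control who later takes acupuncture, it does not say whether events from Weeks 0 to 6 are counted, or whether they are shown under waitlist or under acupuncture. Untreated and treated time could be pooled.

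**Comparison.** With all randomised participants as the safety set, the Week 0 to 6 comparison has up to 44 acupuncture and 44 waitlist participants, whatever the later uptake.

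**The case against.** The strongest reply is that this is loose wording. The waitlist arm is described under the general heading Interventions (2.7), so the word in section 2.9 might mean the allocated condition, and everyone would be in the set. That may be what the authors intend. The text nevertheless runs against it: section 2.7.2 says controls receive no study-specific intervention, and section 2.9 itself uses the word for something that can be discontinued and can cause an event. The ambiguity would need correcting in any case.

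The second reply is that little is lost. Much of this stands. Adverse events and C-SSRS are scheduled in both arms, serious events go to the ethics committee, and sections 2.3.3 and 2.12 say that withdrawals and their reasons are documented and dealt with in the final analysis. A reader might infer that serious events in untreated controls would vanish from the report. The documents do not support that. What they support is narrower: such events would sit outside any table built on the safety set.

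A reader might also infer that worsening mood could not be separated from an effect of acupuncture. That does not follow either. MADRS is the primary outcome, analysed by assigned arm in all randomised participants, and MDS-UPDRS III is analysed as a secondary outcome collected in both arms (section 2.10). Mean change on both scales keeps its randomised comparison.

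The third reply is that adverse event table layouts belong in an analysis plan that is not shown. That is right for the layouts, and their absence is not criticised here. The membership rule is different, because the article states it and it does not suit the design.

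**Conclusion.** The point stands as a badly fixed definition of the safety set. On the plain wording, control membership depends on uptake of treatment offered after the controlled period. Between 0 and 44 of 44 controls enter. At any uptake below 100% they are a post-randomisation selection that leaves out anyone who withdrew before a session or declined. The outcomes affected are adverse event and serious adverse event incidence, falls, hospitalisation and C-SSRS findings. The primary analysis is not touched.

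Two stronger readings should be avoided. One is that the Week 0 to 6 safety comparison is necessarily 44 against 0. That adds a time limit which section 2.9 does not contain: it is the result only if uptake is nil or if membership is judged at Week 6. The other is to take the 20% dropout allowance in section 2.4 as a forecast of how many controls will be lost from the set, and to suppose that they are mainly those who deteriorated. The allowance is a planning figure for both arms, and the documents say nothing on its timing or on how the reasons for dropout would be distributed.

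The conclusion rests on reading intervention as study treatment, which the article's own usage favours, and on uptake being unknown.

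**What to change.** Define the safety set as all randomised participants, grouped by the condition actually received in Weeks 0 to 6 (acupuncture or waitlist). Compare adverse events, serious adverse events and C-SSRS findings by arm for Weeks 0 to 6 as the controlled safety comparison. Report control-arm events after first acupuncture separately, so that untreated and treated time are not pooled.

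The cost is one changed definition and some extra tabulation. No new data, visits or participants are needed, because Table 1 already schedules adverse events and C-SSRS in both arms at every visit. The change should be made before database lock.

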#### Dropout and discontinuation criteria

2.3.3

Participants will be withdrawn from the study if any of the following criteria are met. The reason for withdrawal will be documented in detail and included in the final analysis. Withdrawal will not affect access to routine clinical care.

Occurrence of a serious adverse event (SAE), or significant worsening of psychiatric symptoms, defined as either (1) an increase in the MADRS total score of more than 50% compared with baseline, or (2) the emergence of clinically significant suicide risk as assessed by the Columbia–Suicide Severity Rating Scale (C-SSRS), or the development of a serious concomitant illness, if the investigator deems continuation inappropriate.

Clinically significant motor worsening is additionally defined as safety-driven deterioration requiring urgent escalation of antiparkinsonian therapy (e.g., new initiation or a clinically necessary substantial dose increase), hospitalization for motor complications, or recurrent injurious falls requiring medical attention; when feasible, a clinically meaningful increase in the MDS-UPDRS III score will be recorded to support documentation.

Inability to continue due to poor adherence, frequent missed visits, or loss to follow-up (e.g., failure to complete ≥2 consecutive follow-up visits).

Any other circumstance deemed unsuitable for continued participation based on a comprehensive assessment by the study team.

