#### Acupuncture group

2.7.1

In addition to their standard pharmacotherapy, participants assigned to the acupuncture group will receive a standardized acupuncture intervention. The treatment protocol consists of 18 sessions, administered three times per week over 6 weeks.

All procedures will be performed by licensed physicians with at least 3 years of clinical acupuncture experience. Prior to the trial, all acupuncturists must complete standardized training and pass an assessment to ensure procedural consistency. To ensure continuity, each participant will be treated by the same acupuncturist throughout the intervention period.

Acupoint Prescription and Needles:

The selected acupoints are: Sishenzhen(four points located 1.5 cun anterior, posterior, and lateral to GV20), Shenting (GV24), Yintang (GV29), Neiguan (PC6, bilateral), Shenmen (HT7, bilateral), and Sanyinjiao (SP6, bilateral). Please refer to **Figure 2** for the location of the related acupoints.

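### The psychiatric-worsening criteria rest on MADRS and C-SSRS, but Table 1 schedules neither scale, nor an adverse-event query, between Week 0 and Week 6, and the arms differ in scheduled contacts (18 against 0)

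*Protocol article*

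**What the plan says.** Section 2.3.3 withdraws a participant for significant worsening of psychiatric symptoms and defines it in two ways: "an increase in the MADRS total score of more than 50% compared with baseline", or "the emergence of clinically significant suicide risk as assessed by the" C-SSRS. The same section has criteria that need neither scale: a serious adverse event, a serious concomitant illness, motor worsening, and a general clause for any other unsuitable circumstance.

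Table 1, headed "Schedule of enrollment, interventions, and assessments", ticks MADRS and C-SSRS at screening, W0, W6, W8, W12 and W24. The row for adverse events and concomitant medications has the same ticks. Vital signs are taken at W0 and W6.

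Section 2.9 says the C-SSRS "will be used to systematically assess suicide risk during the screening period and at each follow-up point", which agrees with Table 1. It also says: "Safety monitoring and assessment will be conducted throughout the study". It names no visit, instrument or frequency between W0 and W6.

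For the acupuncture arm, section 2.7.1 states: "The treatment protocol consists of 18 sessions, administered three times per week over 6 weeks". Section 2.7.2 gives the waitlist arm no study intervention in those six weeks, and the checklist for outside treatments is used only at assessment visits. It also allows antidepressant changes during the trial when symptoms worsen.

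**The concern.** A criterion defined by a scale score needs a score. In the six weeks when controls wait and both arms are asked to keep medication as stable as possible, the schedule supplies none. The protocol foresees worsening in this period, because section 2.7.2 allows for treating it, but describes no scheduled way of finding it. The general statement in section 2.9 and the timetable in Table 1 therefore do not match for the period that matters most to the trial.

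The second issue is how events are ascertained. Acupuncture participants are seen three times a week, and a needling reaction, a new symptom or a medication change can come up at any session. Controls have no scheduled occasion to mention such things until W6, when they must recall six weeks. If events from both sources are pooled and tabulated by arm, part of any difference will reflect how often people were seen.

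**Working it through.** **Inputs**
- Time points carrying MADRS, C-SSRS and the adverse-event/medication row: screening, W0, W6, W8, W12, W24 (Table 1).
- Sessions: 3 per week for 6 weeks (section 2.7.1).
- Scheduled waitlist contacts between W0 and W6: none in Table 1 or section 2.7.2.
- Baseline MADRS range: 7 to 34 (section 2.3.1).

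**Step 1. The plan's own session count.** 3 × 6 = 18, which agrees with section 2.7.1.

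**Step 2. Scheduled readings inside the controlled period.** Of the post-screening time points 0, 6, 8, 12 and 24, those strictly between 0 and 6 number 0. The gap is 6 × 7 = 42 days. It applies equally to both arms, so to all 88 planned participants, and to the adverse-event/medication query as well as the two scales.

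**Step 3. Does the MADRS criterion need a new score?** Yes. It is met when the total exceeds 1.5 × baseline:
- baseline 7: above 1.5 × 7 = 10.5, a rise of more than 3.5 points;
- baseline 20: above 1.5 × 20 = 30, a rise of more than 10 points;
- baseline 34: above 1.5 × 34 = 51, a rise of more than 17 points.

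The threshold depends on the person's own baseline, so it cannot be judged without administering the scale. The C-SSRS criterion likewise names its instrument. The first scheduled post-baseline occasion for either is W6, which closes the controlled period.

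**Step 4. Scheduled contacts between W0 and W6.** Acupuncture 18, waitlist 0.

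**Step 5. What the 18 contacts contain.** Table 1 attaches no MADRS, C-SSRS or adverse-event query to them, and section 2.6 keeps acupuncturists out of outcome assessment. The imbalance is therefore in the opportunity for events and medication changes to be noticed or mentioned. It is not in scale measurement, which is absent from the schedule in both arms.

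**The case against.** Table 1 lists scheduled assessments and does not forbid others. Section 2.9 makes a general commitment to monitoring, section 2.7.2 allows a response to worsening, and several withdrawal criteria need no scale. Section 2.3.2 excludes significant suicide risk at entry. This stands. A reader might infer that the psychiatric criteria cannot operate before W6, but the documents do not support that: an unscheduled MADRS or C-SSRS could be done, and the criteria would then apply. What they support is that no reading is scheduled.

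A reader might also infer that the rule produces more withdrawals before W6 in one arm and so biases the primary analysis. The documents do not support this either. Scheduled scale measurement is equally absent in both arms, and the sessions carry no scale, so the rule as written gives no basis for claiming differential withdrawal.

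Third, sections 2.9 and 2.10 state no between-arm comparison of adverse events. The safety set, defined by receipt of at least one intervention, read literally leaves out controls before W6, and tabulation is commonly left to an analysis plan. So the reporting point is conditional: it concerns any such summary that is made. It is still worth fixing in advance, because the unequal contact is built into the design and the limitations in the Discussion do not mention it.

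Lastly, this is a condensed article, and interim safety contacts may be described in the full protocol. But section 2.1 presents Table 1 as the schedule for all interventions, assessments and follow-up visits. The point compares a stated rule with a stated schedule and does not rely on an omitted detail.

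**Conclusion.** The point holds in a limited form. Over 42 days, in both arms, there are 0 scheduled readings of the two scales that define psychiatric worsening and 0 scheduled adverse-event or medication queries, although section 2.9 describes monitoring without a break. The first scheduled reading after baseline that can meet the criteria is the primary endpoint visit. Scheduled contacts before that visit are 18 against 0, which gives adverse events and medication changes unequal opportunity to be noticed.

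This assumes that Table 1 is complete, as section 2.1 indicates. The documents give no detection rates, so the effect of unequal contact on event counts cannot be quantified; its direction would be towards more recorded events in the acupuncture arm. No conclusion follows about bias in the MADRS comparison. The matter should be put right, but it does not invalidate the primary analysis.

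**What to change.** Reconcile Table 1 with sections 2.3.3, 2.7.2 and 2.9, so that the schedule and the psychiatric-worsening criteria agree for W0 to W6, with the same timing and method in both arms. Which clinical rule and which timing to adopt is for the sponsor to decide. If readings are added, the text should say how assessor blinding under section 2.6 is protected and whether extra MADRS scores enter the repeated-measures model.

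Separately, state that any between-arm adverse-event summary for W0 to W6 uses only events elicited by the same scheduled question in both arms. Events noted at needling sessions should be reported separately, within the acupuncture arm.

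The reconciliation is a text change, plus whatever staff time the sponsor's choice entails. The reporting rule is one sentence. Its small downside is that the between-arm table will hold fewer events; those noted at sessions are still reported in their own table.
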